### Protocol development and post implementation phases

During this phase, data will be collected for children presenting to the ED with brain attack symptoms relevant for stroke.

For secondary aim (4), in participants with confirmed stroke, the health economic impact will be determined using the Child Health Utility-9D (CHU-9D) as a paediatric generic preference-based measure of health-related quality of life, to allow calculation of quality-adjusted life years (QALYs) in cost-utility analyses.^42^ Data will be entered into a REDCap database (table 1).

For secondary aim (5), the Paediatric Stroke Outcome Measures^40^ and the paediatric version of the modified Rankin Scale^41^ will be derived where possible if data are available for the retrospective patient cohort in the pre-implementation phase, and prospectively collected in the protocol development and post implementation phases.

The full list of data variables collected is detailed in online supplemental e-Table 2.

## Sample size and power calculations

We anticipate 326 patients with suspected stroke will be recruited during the protocol development and prospective phases of the study (based on numbers of patients recruited to institutional stroke registries in Victoria and New South Wales). Recent literature suggests that approximately one in three children with stroke symptoms will have a final diagnosis of stroke following imaging.^31
43–45^ Therefore, we anticipate 98 participants with a radiologically confirmed diagnosis of stroke in each study phase. Estimates of pre-implementation time to stroke diagnosis are based on extrapolation of local published data^13^ and audit data provided by three study sites. Estimates of post implementation time to stroke diagnosis are based on audit data from Queensland Children’s Hospital, where the proportion of children diagnosed within 4.5 hours increased from 15% to 40% during the 12-month period following introduction of their institutional PACS in 2019. We estimate that 15% of children will be diagnosed within 4.5 hours in the pre-implementation phase, increasing to 40% in the post implementation phase.

The *primary outcome* is the change in the proportion of children with stroke diagnosed within a 4.5-hour time window for reperfusion therapies, pre- and post-PACS implementation (figure 4). Time to diagnosis will be based on radiological confirmation of ischaemic infarction or haemorrhage on CT or MRI. This will be determined by calculating the time elapsed from last seen well to completion of neuroimaging, which is electronically recorded on imaging studies.

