## Methods and analysis

### Study design

A quasi-experimental, two-tiered preintervention and postintervention study design will be used to evaluate the effects of the study interventions in tertiary children’s hospitals in Australia and New Zealand. The pre-implementation phase is the 3-year period from 2015 until 2017, reflecting the era prior to the launch of the Australian guideline for the acute management and diagnosis of stroke in children.^28^ The combined protocol development and post implementation phases are from 2018 to 2026. The study will follow the Transparent Reporting of Evaluations with Non-randomised Design statement for quasi-experimental non-randomised trials.^32^

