**Figure 4 F4:**
[figure not shown]
PACS study outcome measures and analyses. AIS, arterial ischaemic stroke; AuSCR, Australian Clinical Stroke Registry; BASICS, Brain Attack and Stroke in Children Screen; ED, emergency department; EMS, emergency medical services; PACS, Paediatric Acute Code Stroke; ROC, receiver operating characteristic; tPa, tissue plasminogen activator.

Due to the hospital-based nature of the proposed intervention, when powering this study, we have taken appropriate care of the hierarchical nature of the data, where individual patients are clustered within the treating hospitals. It is therefore appropriate to anticipate the presence of a design effect (expressed through the value of the intraclass correlation coefficient), as would have to be done in the situation of cluster-randomised studies. In addition, different hospitals will be able to recruit different numbers of patients, thus there will be a variation of cluster sizes.

Nine hospitals are participating in the study. At the time of receiving grant funding in July 2020, seven hospitals had agreed to participate in the study. Based on this consideration, assuming the settings of alpha=0.05, the intraclass correlation coefficient of 0.05 (corresponding to a small-to-medium hospital-specific effect) and the coefficient of variation of hospital-based cluster sizes of 0.5 (medium-to-high level of variation) with at least seven hospitals, recruiting the 98 patients with radiologically confirmed diagnosis of stroke in the pre-PACS implementation phase and 98 patients in the post-PACS protocol implementation stage (on average 14 patients per hospital for both pre-implementation and post implementation stages), will yield 80% power to detect a change from 0.15 to 0.40 in proportion of children diagnosed within 4.5 hours of symptom onset.

In addition, this sample size will be sufficient for further validation and continuous updating of the BASICS tool in order to further improve its predictive capacity (as the total number of screened patients is expected to be at least three times the number of confirmed strokes).^30
31^

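### The 326 suspected cases support one cohort of about 98 strokes over development plus prospective recruitment, not 98 in each phase: the pre-phase 98 has no stated basis and the post-phase 98 mixes exposed and unexposed children

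*Protocol article*

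**What the plan says.** The Sample size and power calculations section of the protocol article starts from an expected recruitment: "We anticipate 326 patients with suspected stroke will be recruited during the protocol development and prospective phases of the study". It adds that "approximately one in three children with stroke symptoms will have a final diagnosis of stroke following imaging", and from these two statements concludes that "we anticipate 98 participants with a radiologically confirmed diagnosis of stroke in each study phase".

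The power statement in the same section then uses 98 twice. One is for the baseline, "recruiting the 98 patients with radiologically confirmed diagnosis of stroke in the pre-PACS implementation phase", and the other is "98 patients in the post-PACS protocol implementation stage", described as "on average 14 patients per hospital for both pre-implementation and post implementation stages". With these numbers it claims 80% power for a change from 0.15 to 0.40.

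On the phases, Study design says: "The combined protocol development and post implementation phases are from 2018 to 2026". Table 1 heads everything from 2018 onwards as post implementation. Study participants and Data collection define the baseline as strokes already confirmed radiologically, found retrospectively by ICD-10 code for 2015–2017. The Interventions section says that five of the nine hospitals had no established Code Stroke protocol at commencement and that four did. The primary model in the Data analysis plan has a single fixed effect for implementation phase.

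**The concern.** Two things go wrong between the 326 and the power statement.

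First, one recruitment figure is made to supply both phases. The 326 are recruited from 2018 onwards, so they can say nothing about how many strokes occurred in 2015–2017. A suspected-to-confirmed yield cannot apply to a cohort that is identified by confirmed-stroke codes. The article gives no other source for the baseline count.

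Second, the 98 that do follow from 326 span protocol development and post-implementation recruitment, yet the power statement assigns all of them to the post-implementation stage. At the five hospitals that started without a protocol, some of these children presented before there was one to activate. The 40% expected in the post phase comes from a hospital in the 12 months after it introduced its protocol, so it describes exposed children only.

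The stated power rests on 98 exposed strokes at 40%. As written, either the exposed number is smaller or the 40% is applied to children who did not have the intervention.

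**Working it through.** **Inputs from the article.** 326 suspected cases; yield about one in three; 98 per phase; 14 per hospital; seven hospitals in the calculation and nine participating; ICC 0.05; coefficient of variation of cluster size 0.5; alpha 0.05 (taken as two-sided, as sidedness is not stated); 0.15 versus 0.40.

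**Assumptions.** The article prints no design-effect formula, so the standard one for unequal clusters is used. The share of strokes before go-live, and a rate of 15% in those children, are also assumed.

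**1. Reproducing the requirement.**
- Two proportions, 0.15 versus 0.40, 80% power: 49 per phase without clustering.
- Design effect = 1 + [(1 + CV²)m − 1] × ICC = 1 + (1.25 × 14 − 1) × 0.05 = 1.825.
- 49 × 1.825 = 89.4; 89.4/14 = 6.4, rounded up to 7 hospitals; 7 × 14 = 98.
- Effective size 98/1.825 = 53.7 per phase. Power is 83.7% by normal approximation and 79.2% with a noncentral t on 12 df.

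The requirement of 98 per phase for about 80% power therefore reproduces.

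**2. What 326 delivers.**
- 326 × 0.30 = 97.8, so about 98 strokes in total over development plus prospective recruitment.
- Two phases need 2 × 98 = 196, and 196/326 = 60%, far from the stated yield. The 326 can supply one cohort only.

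**3. Pre-go-live strokes excluded from the post phase** (pre-phase kept at 98; design effect recomputed for the smaller post-phase clusters):

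| Assumed share before go-live | Post strokes | Power, 7 hospitals (normal) | Power, 7 hospitals (t, 12 df) | Power, 9 hospitals (normal) |
|---|---|---|---|---|
| 0% | 98 | 84% | 79% | 88% |
| 10% | 88 | 83% | 78% | 87% |
| 25% | 74 | 81% | 75% | 85% |
| 50% | 49 | 76% | 67% | 79% |

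**4. Pre-go-live strokes counted as post at 15%.** With share f, the post proportion is 0.40 − 0.25f, with 98 still in each phase:

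| f | Post proportion | Power, 7 hospitals (normal) | Power, 7 hospitals (t, 12 df) | Power, 9 hospitals (normal) |
|---|---|---|---|---|
| 10% | 37.5% | 76% | 71% | 81% |
| 25% | 33.75% | 62% | 57% | 67% |
| 50% | 27.5% | 35% | 31% | 39% |

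For nine hospitals, m = 98/9 = 10.9 and the design effect is 1.63, giving an effective size of 60.1 per phase.

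**The case against.** The strongest reply is that Study design and Table 1 treat 2018 onwards as one block, and Table 1 calls it post implementation. On that labelling 326 × 30% does give 98 post-phase strokes, and four hospitals already had protocols at commencement. This stands as a point about the count: a reader might infer that the 98 post-implementation strokes will not be reached, and the article does not show that. But the reply moves the problem. If the label governs, children seen before their hospital had a protocol count as exposed, and that costs more power than leaving them out.

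It also stands that exclusion alone costs little. By normal approximation with seven hospitals, power stays at or above 80% down to 69 post-phase strokes, a loss of 29 of the 98. The large drops need heavy dilution at an assumed 15%. Nine hospitals rather than seven soften every figure.

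It can also be said that classification by go-live date belongs in a full protocol or analysis plan. The detailed rule may well sit there. The conflict between the derivation, the power statement and the Table 1 label is nevertheless in this article.

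Three further inferences are not supported:
- One third of 326 is nearer 109, but the article says approximately one in three, and 98 is the more cautious figure.
- Annual stroke counts in the two periods cannot be compared. Entry criteria differ, with a 24-hour symptom limit stated only from 2018, and site approvals ran from August 2021 to September 2023.
- Nothing says that the retrospective cohort will be capped at 98.

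**Conclusion.** The concern holds in a limited form. The 326 support about 98 strokes in total from 2018 onwards, and the conclusion of 98 in each phase does not follow from them. The baseline 98 has no stated basis. The post-phase 98 combines development-period and post-implementation children, although five of nine hospitals began without a protocol.

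The size depends on a split that the article does not give. With seven hospitals and the normal approximation, an assumed 10% to 50% before go-live takes power from about 84% to between 83% and 76% if those children are excluded. If they are counted as post at an assumed 15%, it falls to between 76% and 35%. With nine hospitals the ranges are 87% to 79% and 81% to 39%. The t-based version starts at 79%, so on that basis there is no reserve.

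The documents do not show that the study is underpowered. They show that the stated power is not tied to the number of exposed children, and that the phase definition decides whether the loss is small or large.

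**What to change.** Four changes to the sample size section and the phase definition:

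1. Define post-implementation in the primary model by each site's go-live date, so that children seen before it are not counted as exposed, and bring the Table 1 column label into line.
2. State the expected number of confirmed strokes after go-live separately from the number expected during protocol development.
3. Base the pre-phase number on the count of confirmed strokes for 2015–2017, not on the 326.
4. Restate power for those two numbers, giving the design-effect formula and the number of hospitals used.

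The cost is some rewording and one recalculation, with no additional patients. The downside is that the stated power may be slightly lower.

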### Study participants, inclusion and exclusion criteria

During the pre-implementation phase, from 2015 to 2017, children aged 1 month to 18 years with radiologically confirmed stroke will be retrospectively identified from ICD10 principal diagnosis codes for stroke and then medical record review.

During the Code Stroke protocol development and post implementation phases from 2018 to 2026, children aged 1 month to less than 18 years of age with symptoms of less than 24 hours duration that are suspicious for stroke (also referred to as brain attacks)^34^ will be eligible for recruitment to the PACS study. Symptoms include altered consciousness; focal face arm or leg weakness; dysarthria; dysphagia; sensory disturbance; visual disturbance; limb incoordination/ataxia; visual/sensory neglect; pupillary abnormality; severe headache with associated focal neurology and seizure(s) with associated focal neurology^28^ (figure 1). Patients will be categorised into two final diagnostic groups: stroke or mimics, based on presence or absence of acute ischaemic or haemorrhagic infarction on brain imaging. Stroke will be further sub-categorised into AIS or haemorrhagic stroke (HS) as adjudicated by a paediatric radiologist. Children with acute neurological symptoms that are not relevant for stroke will be excluded from the study.

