### Interventions

#### Code Stroke protocol development and implementation (all PACS sites)

A Code Stroke protocol^35
36^ is a hospital-based protocol and multidisciplinary emergency response system designed to standardise initial clinical assessment and urgent imaging of children with suspected stroke, informed by evidence-based guidelines.^28
29^ Components along the process of care, which begins on arrival in the ED, include recognition of symptoms associated with stroke^37^ at the time of triage, which leads to activation of Code. This triggers rapid clinical assessment by ED physicians. Neurologists will confirm the presence of neurological signs and assess the severity of symptoms using the paediatric adaptation of the National Institutes of Stroke Severity Scale (pedNIHSS),^38^ and in the context of ischaemic stroke, to screen children for eligibility and contraindications to reperfusion therapies, which includes collection of bloodwork. The clinicians decide the need for and type of brain imaging (CT or MRI) to confirm stroke diagnosis. Imaging leads to decisions about reperfusion therapies for ischaemic stroke or neurosurgical intervention for HS. An example of a Code Stroke pathway is presented in figure 1.

The five tertiary paediatric hospitals without established institutional Code Stroke protocols at commencement of the study will develop and implement the protocols through establishment of multidisciplinary working groups including—but not limited to—paediatric ED physicians, neurologists, neurosurgeons, radiologists, stroke research nurses, anaesthetists, intensivists, haematologists and neuro-interventional radiologists. Current practice will be evaluated through engagement of these stakeholders, and site-specific analysis of barriers and enablers to improving stroke diagnosis will be identified, drawing on previous conceptual modelling using Value Focused Process Engineering to map the process of care in children with suspected stroke.^39^

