## Data collection

### Pre-implementation and pre-protocol development phase

All sites will retrospectively collect data for confirmed strokes by case record review from 2015 to 2017, using the ICD-10 codes: I61.0–I61.6, I61.8, I61.9, I62.9, I63.0–I63.6, I63.8, I63.9, I64.0 and G45, for the primary aim of determining time to diagnosis prior to implementation of Code Stroke protocols across study sites (table 1).^40
41^

**Table 1 T1:** Data to be collected

Variables	Pre-implementation (2015–2017) confirmed stroke	Post implementation phase (2018 onwards) stroke	Post implementation phase (2018 onwards) mimics
Demographics	✓	✓	✓
Prehospital care*	✓	✓	✓
Presenting clinical features	✓	✓	✓
pedNIHSS (baseline, 24 and 48 hours)	✓†	✓	✓‡
EMS call taker and paramedic coded diagnoses*	✓	✓	✓
Sensitivity of ED physician diagnosis		✓	✓
Time to diagnosis§	✓	✓	✓
Timelines of care (pre- and post-arrival)	✓	✓	✓
Length of stay, acute hospital and inpatient rehabilitation	✓	✓	✓¶
Follow-up phone call following ED discharge for mimics to confirm no change in diagnosis		✓	✓
Rates of reperfusion therapy use (t-PA and ECR)	✓	✓	
Reperfusion therapy related serious adverse events	✓	✓	
Neurological outcomes: Outcomes: (PSOM and mRS) at discharge 7, 30 and 90 days. mRS at 30 and 90 days	✓	✓	
Child Health Utility (CHU-9D)		✓	
Costs of childhood stroke, using hospital/Medicare linked services health utilisation cost data		✓	

* For the subgroups of children transported to ED by ambulance.

† Paediatric version National Institutes of Health Stroke Scale (pedNIHSS) and Paediatric Stroke Outcome Measures (PSOM) may be derived retrospectively in some (but not all) patients from clinical assessment notes and should be collected if applicable.

‡ Only at baseline.

§ Time to diagnosis will be collected for all children presenting to the emergency department, regardless of mode of arrival and for inpatients where a Code Stroke is activated.

¶ Only if admitted.

ECR, endovascular clot retrieval; ED, emergency department; EMS, emergency medical services; mRS, modified Rankin score; tPA, tissue plasminogen activator.

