## Data analysis plan

### Outcomes

The *primary outcome* is the change in the proportion of children with stroke diagnosed within a 4.5-hour time window for reperfusion therapies, pre- and post-PACS implementation. This will be estimated using a mixed-effect logistic regression model with the dichotomous variable ‘diagnosed within 4.5-hour time window (yes/no)’ as the dependent variable, implementation phase as an independent fixed effect and hospitals as random effects.

*Secondary outcomes* (figure 4) include:

The proportion of children receiving reperfusion therapies will be analysed as for the primary outcome.Accuracy of emergency medical services (EMS) call taker, paramedic and ED physician stroke diagnosis against the gold standard diagnosis of radiologically confirmed stroke. Change in correctness of stroke (vs mimic) diagnosis, pre-implementation and post implementation of PACS will be estimated using a random-effect logistic regression model with dichotomised correctness of diagnosis as the dependent variable, intervention phase as an independent variable and hospital as a random effect.The impact of EMS call taker, paramedic and ED physician actions (eg, lights/sirens response and prenotification, PACS activation, MRI selection as the first imaging study in suspected AIS) on time to diagnosis will be analysed. Differences in times will be analysed using clustered quartile regression, with hospitals as clusters.The economic impact of shorter time to diagnosis, increased utilisation of MRI imaging and increased rates of reperfusion therapy in stroke patients will be measured using the CHU-9D, and hospitals linked services health utilisation and cost data.

Markov cohort model will be developed to quantify per-capita, national healthcare and societal costs economic costs, and the associated lifetime loss of QALYs and life years.

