Limitations include bias related to the mixed retrospective and prospective data collection. Different hospitals will be able to recruit different numbers of patients, thus there will be variation in cluster sizes. Protocols are being developed and tested in tertiary hospitals but approximately 50% of children with stroke initially present to non-tertiary paediatric hospitals.^9^ Therefore, an important priority for future research is to adapt Code Stroke protocols developed in the PACS study to rural and regional centres. Stroke telemedicine will be an important component of this initiative.^50^ These future approaches will ensure that all children with stroke, no matter where they reside or to which health setting they present, will have access to coordinated systems of acute stroke care, to technologies that facilitate rapid diagnosis and to reperfusion therapies that limit the extent of brain injury.

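### The non-randomised primary comparison is modelled with phase and hospital only, so a change in stroke type or pre-arrival time between phases can enter the estimated effect of Code Stroke

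*Protocol article*

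**What the plan says.** - **Design.** Study design: "A quasi-experimental, two-tiered preintervention and postintervention study design will be used". The pre-implementation phase is 2015 to 2017; protocol development and post-implementation run from 2018 to 2026.
- **How the cohorts are found.** Under Study participants, pre-implementation cases are confirmed strokes found retrospectively by principal ICD-10 code and record review, and no limit on symptom duration is stated. From 2018, children are eligible if symptoms suspicious for stroke have lasted under 24 hours.
- **Outcome.** Sample size and power calculations defines time to diagnosis by "calculating the time elapsed from last seen well to completion of neuroimaging".
- **Where the intervention starts.** The Code Stroke section describes "Components along the process of care, which begins on arrival in the ED".
- **Primary model.** Outcomes specifies a mixed-effect logistic regression "with the dichotomous variable ‘diagnosed within 4.5-hour time window (yes/no)’ as the dependent variable", with "implementation phase as an independent fixed effect and hospitals as random effects". The Abstract repeats this model. No patient-level covariate and no adjusted sensitivity analysis is named.
- **Data available.** "Stroke will be further sub-categorised into AIS or haemorrhagic stroke (HS) as adjudicated by a paediatric radiologist"; for the retrospective cases, the listed ICD-10 codes separate I61 from I63. Table 1 ticks the row "Timelines of care (pre- and post-arrival" for strokes in both phases.

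**The concern.** In a before-and-after comparison the phase coefficient carries everything that changed between the cohorts. A hospital random effect absorbs stable differences between sites. It does not remove a change over time in which patients are counted.

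Two patient factors matter here. First, the clock includes time before arrival. An ED presenter who arrives after 4.5 hours without earlier imaging fails the outcome whatever the hospital does. Second, the Introduction notes that CT is poor at showing infarction in ischaemic stroke, so stroke type plausibly affects how soon the diagnosis is confirmed.

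The cohorts are found by different routes, and the stated 24-hour limit applies to one of them only. A difference in pre-arrival time is therefore partly built in, in the direction that favours the later phase. What is at stake is whether the reported change in proportion can be attributed to Code Stroke.

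**Working it through.** **Inputs from the protocol:** 98 confirmed strokes per phase, 7 hospitals, 14 per hospital per phase, ICC 0.05, coefficient of variation of cluster size 0.5, alpha 0.05 (taken as two-sided), 15% against 40%. **Not in the protocol, and assumed below:** stroke-type mix, arrival-time distribution and success rates by stratum.

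**1. The plan's own power figure.** Design effect = 1 + [(1 + 0.5²) × 14 − 1] × 0.05 = 1.825. Effective n = 98 / 1.825 = 53.7 per phase. Power for 15% against 40% is 83.7% by the normal approximation, 77.5% with continuity correction, and 79.2% with a t distribution on 2 × 7 − 2 = 12 df. The stated 80% is reproduced. The issue is bias, not power.

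Steps 2 to 4 assume **no true effect** of Code Stroke. The last column of each table is the chance of a significant result in favour of the later phase at effective n 53.7 (nominal 2.5%).

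**2. Stroke type.** Assume 30% of haemorrhagic and 5% of ischaemic strokes are diagnosed in the window, with a 40% haemorrhagic share before: 0.40 × 0.30 + 0.60 × 0.05 = 0.15. The spurious shift is the change in share × 0.25.

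| Haemorrhagic share after | Proportion after | Shift | False favourable |
|---|---|---|---|
| 50% | 17.5% | +2.5 | 5% |
| 60% | 20.0% | +5.0 | 10% |
| 80% | 25.0% | +10.0 | 25% |

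The last row needs the share to double. A fall in the share gives shifts of the opposite sign.

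**3. Arrival time.** Assume 40% arrive within 4.5 hours before, and 37.5% of those are diagnosed in time: 0.40 × 0.375 = 0.15.

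| Arriving within 4.5 h after | Proportion after | Shift | False favourable |
|---|---|---|---|
| 50% | 0.50 × 0.375 = 18.8% | +3.8 | 8% |
| 60% | 0.60 × 0.375 = 22.5% | +7.5 | 17% |

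**4. The 24-hour limit on one phase only.** This is one particular source of an arrival-time shift. If a fraction f of pre-phase children had symptoms beyond 24 hours, none of them can meet the outcome. The pre-phase rate on the later eligibility rule is then 0.15 / (1 − f).

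| f | Comparable pre rate | Shift | Share of 25 points | False favourable |
|---|---|---|---|---|
| 10% | 16.7% | 1.7 | 7% | 4% |
| 20% | 18.8% | 3.8 | 15% | 8% |
| 30% | 21.4% | 6.4 | 26% | 14% |
| 50% | 30.0% | 15.0 | 60% | 46% |

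The Introduction says diagnostic delay is sometimes longer than 24 hours. That is delay to diagnosis rather than to arrival, so it does not fix f. The 50% row is an outer bound for illustration.

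**5. Does adjustment remove the artefact?** In step 2 the rates within stroke type are 30% and 5% in both phases, so the effect adjusted for type is nil. In step 3, restricting to arrivals within 4.5 hours gives 0.15 / 0.40 = 0.188 / 0.50 = 0.225 / 0.60 = 37.5% in both phases. In step 4, applying the limit to both phases equates the rates.

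**The case against.** **What stands.**
- Every size above rests on assumed case mix, and the direction of a stroke-type shift is unknown.
- Time before arrival is not always untouched by the programme. The protocols also target inpatients, for whom onset-to-arrival is not defined in the same way. The four hub hospitals partner with ambulance services, so arrival time there may be partly a mediator, and adjusting for it could remove real benefit.
- Because late arrivers almost never succeed, a crude arrival term invites separation.
- Starting the clock at last seen well fits the treatment window the study is about and is not itself an error.
- The Discussion acknowledges bias from combining retrospective with prospective data.

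**What does not stand.** Covariates are often left to an analysis plan, and one may exist. But the article writes out the primary model and gives it a single fixed effect, so this is a stated choice. Acknowledging bias in the limitations does not remove it from the estimate.

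**Stronger readings a reader might infer.**
- *That stroke type and arrival delay mostly determine the outcome.* No figure supports this, and the Introduction ranks in-hospital factors above prehospital ones as causes of delay.
- *That half the cohort are transfers whose times cannot change*, so that 40% overall needs (0.40 − 0.5 × 0.15) / 0.5 = 65% among direct presenters. The Discussion says only that "approximately 50% of children with stroke initially present to non-tertiary paediatric hospitals". That describes where children first present, not the make-up of the study cohort. Nor does the article say that children already imaged elsewhere enter the primary set, or name transfer status among the variables collected.

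**Conclusion.** The concern holds in a limited form. The primary comparison is non-randomised, its cohorts are identified differently, and its stated model adjusts for no patient characteristic, although stroke type and pre-arrival timelines appear to be available in both phases. Following that model lets case-mix change enter the phase effect.

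Under the assumed shifts in stroke type or arrival mix, the artefact is about 2.5 to 10 points against a planned 25. The one-sided 24-hour limit contributes 1.7 to 6.4 points if 10% to 30% of pre-phase children were beyond it, and more only at extreme fractions. A reader should not conclude that the planned 25 points could be wholly artefact: no single scenario here reaches it. The shifts could add together or offset one another, and the documents do not allow the actual bias to be estimated.

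**What to change.** 1. Add stroke type (ischaemic or haemorrhagic) as a prespecified fixed effect in the primary model. Expected events are 98 × 0.15 + 98 × 0.40 = 53.9, about 27 per fixed term with phase and stroke type.
2. Prespecify a key sensitivity analysis in ED presenters that applies the same 24-hour symptom limit to both phases. It should also account for onset-to-arrival time, either as a continuous term or by restricting to arrivals within 4.5 hours.
3. If transfer status turns out to be collected, add it to that sensitivity analysis only. The primary population then stays as planned.
4. Report arrival-to-diagnosis time before and after as a supporting outcome; the timelines in Table 1 allow it.
5. Report the adjusted change in proportion by standardisation, because the adjusted odds ratio is conditional while the primary outcome is a change in proportion.

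**Cost.** No extra patients or visits; the changes are to the analysis specification and should be made before data collection ends in mid-2026. A few retrospective cases may lack arrival times. The sensitivity analysis uses fewer children than the primary one. Accounting for onset-to-arrival may remove some true effect at the ambulance-partnered hubs, which is why it should remain a sensitivity analysis.
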